| Criteria for evaluation:  Safety: Safety will be assessed by the Clavien-Dindo classification and reporting of Adverse Events.  The maximum tolerated dose of 5-FU will be determined by giving the first 15-30 patients escalating doses of 5-FU. The morbidity of each dose level of 5-FU 24-hour EPIC will be evaluated by the Data Monitoring Committee 30 days post-treatment. A dose level with ≤1/3 or ≤2/6 with 3b-4 Clavien-Dindo morbidity may proceed to the next dose level. Following the dose titration study, all patients will receive the maximum dose of 5-FU. An interim safety evaluation will be performed after the first 140 patients have been randomized and treated with HIPEC or HIPEC in combination with EPIC. The Clavien-Dindo grade 3-5 morbidity is expected to be approximately 0.35 (35%). If the experimental arm’s 95% CI falls within 0.4 or below, the study will be allowed to continue.  Efficacy: Recurrence free survival (RFS) is determined at 12-months post treatment through the HIPEC registry. Postoperative complications rates with-in 30 days, 5-year overall survival and RFS are further determined through the HIPEC registry and quality of life is assessed by questionnaires through the QoL registry. | | |
| **Dosage of Investigational Products:**  The maximum tolerated dose (MTD) of 5-FU will be determined by giving the first 15-30 patients escalating doses of 5-FU. The morbidity of each dose level of 5-FU 24-hour EPIC will be evaluated by the Data Monitoring Committee within 30 days post-treatment. A dose level with ≤1 of 3 patients or ≤2of 6 patients (extended group size) with 3b-5 morbidity may proceed to the next dose level. If the frequency of 3b-5 morbidity is higher, MTD has been passed and the dose of 5-FU in the efficacy study will be the next lower dose level. If MTD is not reached the highest dose level of 5-FU (850 mg/m^2^) will be used. | | |
| Statistical methods:  Recurrence free and overall survival of the two arms will be compared using the parameters: treatment arm, age, PCI, CC score, use of systemic perioperative chemotherapy (neoadjuvant and/or adjuvant), concomitant liver metastases resection, colon or rectal primary tumor, and lymph-node metastasized primary tumor.  QoL will be analyzed by comparing the answers to questions 29 and 30 in QLQ-C30 by Mann-Whitney U test and Freidman’s repeated measures ANOVA test. Specifically, differences between the sexes will be investigated.  Statistical significance will be set at p=0.05. | | |

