### Efficacy study

Figure 2: Flowchart for the efficacy study

| All colorectal cancers with peritoneal metastases | | | | |
| --- | --- | --- | --- | --- |
| ↓  Randomization intraoperatively  ↙ ↘ | | | | |
| **A: Standard HIPEC**  **(70 patients)**   1. Oxaliplatin  - 460 mg/m^2^ (HIPEC)  1. 5-fluorouracil  - 400 mg/m^2^ IV bolus (Intraop)  1. Calcium folinate  - 60 mg/m^2^ IV (Intraop) | |  | **B:** **Intensified HIPEC+EPIC**  **(70 patients)**   1. Oxaliplatin    - 360 mg/m^2^ (HIPEC) 2. Irinotecan    - 360 mg/m^2^ (HIPEC) 3. 5-FU Bolus    - 400 mg/m^2^ IV (Intraop) 4. Calcium folinate 5. 60 mg/m^2^ IV (Intraop) 6. 5-FU 24-hr EPIC  - According to the dose titration study | |
|  | |  | Prophylactic G-CSF postop day 4-8 | |
| ↓ |  | | | ↓ |
| Interim safety evaluation:  Grade 3-5 Clavien-Dindo morbidity comparison | | | | |
| ↓ | | | | |
| **A: Standard HIPEC**  **(163 patients)** | |  | **B:** **Intensified HIPEC+EPIC**  **(163 patients)** | |
| ↓ | |  | ↓ | |
| Primary endpoint:   - 12-month RFS   Secondary endpoints:   - Overall survival and RFS up to 5 years: Through the HIPEC registry - QoL: Through the QoL registry - Morbidity: Through the HIPEC registry | | | | |

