### Interim safety analysis of the Efficacy study

After randomization, the Clavien-Dindo grade 3a-4b morbidity is expected to be approximately 25-35% when treating patients with the dose of 5-FU determined from the dose titration study. During the interim analysis of the efficacy part of the trial, the DMC will use the morbidity rate of the standard arm and compare it to the experimental arm. If all Clavien-Dindo grade 3-4 complications resolve in-hospital and occur at a maximum rate of 40%, the trial will pass the interim review. If complications lead to permanent sequelae or the rate is higher than 40% a detailed review by the safety committee will ensue prior to letting the efficacy study continue. Comparison with the standard arm will assist in determining the risk/possible benefit ratio. In particular, if the mortality rate is increased, it will be grounds for discontinuing the trial. The trial may be allowed to continue despite increased morbidity if the mortality rates are the same and if the morbidity is of a temporary nature, not leading to permanent functional loss. The decision will be made by the DMC. If necessary, dose reduction may be considered in order to continue and complete the efficacy study.

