#### Interim analysis

The Clavien-Dindo grade 3-4 morbidity is expected to be approximately 0.35 (35%) for patients receiving the maximum dose of 5-FU. Allowing for a small increase in morbidity to 0.40 and an accepted 95% confidence interval width of 0.15, at least 66 patients are needed in the experimental arm to determine whether the arm deviates from the expected morbidity rate. The total sample size will be 140 (70 per arm) for an interim trial safety evaluation (circa 50% of trial included). If the Clavien-Dindo grade 3-4 morbidity falls outside of the 40% mark, then a Fisher’s exact test comparison between the standard and experimental arm will be performed together with a mortality comparison. Concerning in-hospital mortality, a maximum rate of 5% will be set. This planned interim safety evaluation will be unpublished. If the morbidity is increased beyond the set mortality limit or the increase is of a more serious nature, the trial will either be discontinued or alternatively, depending on the character of the complications, a lower dose level may be employed.

The overall survival and recurrence free survival will be reviewed during this interim safety evaluation to see if a primary endpoint of overall survival is attainable with increased cohort size instead of 12-month RFS. If attainable depending on inclusion rate, the endpoint will be changed, and a new sample size calculation will be performed. Likewise, a choice between 3 or 5 year follow-up will be made. Alternatively, trial futility will be determined if no differences at all are forthcoming even in the RFS setting. In this case, the trial will close prematurely. A decision to close the trial is made by the sponsor in conjunction with site investigators.

Possible changes of dose level, endpoint, sample size calculation or other substantial changes will be submitted to the MPA and ERA as an amendment to the protocol.

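### Section 13.2.1 ties the interim safety action to morbidity exceeding the mortality limit, and compares deaths between arms only if grade 3-4 morbidity passes 40%

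*Protocol*

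**What the plan says.** The interim safety evaluation takes place at 140 patients, 70 per arm. Section 13.2.1 expects grade 3-4 Clavien-Dindo morbidity of about 35% at the chosen 5-FU dose and sets a 40% mark. If morbidity passes that mark, a Fisher's "exact test comparison between the standard and experimental arm will be performed together with a mortality comparison". A separate sentence adds the mortality limit: "Concerning in-hospital mortality, a maximum rate of 5% will be set". It names no arm and attaches no action. The action sentence follows: "If the morbidity is increased beyond the set mortality limit or the increase is of a more serious nature", the trial is discontinued or, depending on the type of complication, a lower dose level is used.

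Section 12.5.1 describes the same review differently. If grade 3-4 complications all resolve in hospital and "occur at a maximum rate of 40%, the trial will pass the interim review". Otherwise: "If complications lead to permanent sequelae or the rate is higher than 40% a detailed review by the safety committee will ensue". It then says that "if the mortality rate is increased, it will be grounds for discontinuing the trial", without giving a number. It also allows the trial to go on despite more morbidity if mortality is equal between arms and the morbidity is temporary. The decision is the DMC's.

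Figure 2 in section 8.2.2 labels the interim step "Grade 3-5 Clavien-Dindo morbidity comparison", with no 40% condition.

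**The concern.** The action sentence pairs the wrong quantities. Morbidity is compared with a limit set for deaths, and that limit is one seventh of the expected morbidity (5% against 35%). A reader has to guess what was meant, and the 5% cap is left with no stated consequence.

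The condition on the mortality comparison is a second fault. In Table 2 of the protocol death is grade 5, so a death as such does not count towards the grade 3-4 mark that releases the comparison. Deaths could be unevenly distributed while grade 3-4 morbidity stays at or below 40%, and 13.2.1 would then not call for the arms to be compared on mortality.

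This matters because section 12.1 makes the interim the only planned formal DMC safety review in phase III, barring unexpected serious events. Section 5.4 says it stands in place of a phase II trial, and section 16.2 names postoperative mortality as a main ethical concern.

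**Working it through.** The 5% cap is set without a derivation, so there is no figure of the plan to reproduce. The check reads the rules side by side and then works out what they mean at 70 per arm.

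**Inputs.** n = 70 per arm, expected grade 3-4 morbidity 0.35, morbidity mark 0.40 and in-hospital mortality limit 0.05 (all 13.2.1); expected grade 3a-4b morbidity 25-35% (12.5.1). Let X be the number of experimental-arm patients with grade 3-4 morbidity, X ~ Binomial(70, p).

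**1. The action sentence taken literally.** 3/70 = 4.3% and 4/70 = 5.7%, so 5% is exceeded at 4 or more of 70. At p = 0.35 the expected count is 0.35 × 70 = 24.5. P(X ≥ 4) exceeds 0.9999 for p from 0.25 to 0.35. The condition would be met almost surely at the morbidity the protocol expects.

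**2. The two natural corrections.**

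| Correction | Consequence under 13.2.1 | Fit with 12.5.1 |
|---|---|---|
| Morbidity above 40% | Discontinue or lower the dose | 12.5.1 sends this to a detailed review first |
| Mortality above 5% | Discontinue or lower the dose | Agrees: increased mortality is grounds for discontinuing |

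Only the second fits 12.5.1, and only the second gives the cap an action.

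**3. How often 13.2.1 calls for no mortality comparison.** 28/70 = 40.0% and 29/70 = 41.4%, so as a point estimate the mark is passed at 29 or more. The comparison is not called for when X ≤ 28:

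| True grade 3-4 morbidity | P(X ≤ 28) |
|---|---|
| 25% | 0.998 |
| 30% | 0.972 |
| 35% | 0.842 |
| 40% | 0.552 |

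**4. An illustration with assumed counts.** Take 25 of 70 with grade 3-4 morbidity (35.7%) in the experimental arm, and deaths of 5/70 (7.1%) against 1/70 (1.4%) in the standard arm. The cap is exceeded in the experimental arm, but 13.2.1 states no action for that. Morbidity is below 40%, so 13.2.1 does not call for the mortality comparison either.

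**The case against.** The strongest reply is that the DMC would not be misled. The 5% cap is unconditional, so in-hospital deaths must be counted. Section 12.5.1 has the DMC compare morbidity between arms with no 40% condition, and it names increased mortality as grounds for stopping. Section 13.2.1 itself has overall survival reviewed at the interim, and a footnote to Table 3 has those data obtained beforehand. Figure 2 compares grades 3-5, which include death. Section 12.6 brings related fatal events to the DMC. A formal test of deaths at 70 per arm is also weak: two-sided Fisher p is 0.37 for 4 against 1 death and 0.12 for 6 against 1.

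Most of this stands as mitigation. It does not correct the sentence. The mortality statements in 12.5.1 follow the detailed-review step and carry no number. A grade 3-5 composite is dominated by the far more frequent grade 3-4 events. The weakness of the test argues for judgement about the counts, not for leaving the comparison out.

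Four stronger readings are tempting and not supported:

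- **That the DMC would fail to compare deaths in 84% of trials.** The figure describes one conditional sentence in 13.2.1, not everything the DMC will see.
- **That the two corrections lead to opposite outcomes.** They differ mainly in whether a detailed review comes first. Under 12.5.1 that review can itself end in a lower dose or discontinuation.
- **That the cap might apply to both arms pooled.** The text does not exclude it, but the paragraph is built around the experimental arm, and a lower 5-FU EPIC dose is possible only there. Naming the arm is a clarification.
- **That the synopsis rule changes how often the comparison is triggered.** Its condition that the experimental arm's "95% CI falls within 0.4 or below, the study will be allowed to continue" is a continuation criterion for grades 3-5. Nothing uses it to release the mortality comparison. Its difference from the 40% rate is a separate matter.

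**Conclusion.** The point holds and should be corrected. The action sentence in 13.2.1 is wrong as written: it sets morbidity against the 5% mortality limit, is met at the expected 35% morbidity, and leaves mortality above 5% with no linked action. The same section makes the between-arm mortality comparison depend on a morbidity mark that does not count deaths. At the expected 35% the comparison is not called for with probability about 84%, and with probability 97% or more at 30% or below.

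Those probabilities assume 70 evaluable patients in the experimental arm, independent binomial outcomes, and the 40% mark read as a point estimate in that arm. The near-certainty under the literal wording shows that the sentence is a drafting error. A reader might infer that the trial would in fact be stopped on it, but 12.5.1 leaves the decision to the DMC, and nothing suggests it would act that way. The DMC charter is mentioned in 12.4 but not shown. It may add operating detail, but the faulty rule stands in the protocol.

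**What to change.** Reword 13.2.1 in three places:

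1. In-hospital mortality above 5% in the experimental arm (4 or more of 70) is the limit linked to discontinuation or a lower dose level, by DMC decision.
2. Grade 3-4 morbidity above 40% leads to the Fisher comparison and to the detailed DMC review already described in 12.5.1.
3. The between-arm comparison of mortality is always made at the interim, whatever the morbidity rate.

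How the DMC weighs the cap against the comparison can stay with its judgement and the charter. The cost is a few sentences in 13.2.1, with a matching line in 12.5.1. Sample size, patients and data collection do not change.

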## DATA MOnitoring committee

The DMC which will include three external clinical reviewers will be responsible for making decisions on whether to move to the next dose level, as well as making decision to continue the phase III trial efficacy study after the interim safety evaluation (see interim analysis in the statistics section). The work of the DMC will be described in a DMC charter.

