## Determination of sample size

Dose titration study

15-30 patients depending on how many dose levels require 6 patients.

Interim trial safety evaluation

140 patients (70 in each arm) which is close to 50% of the sample size for an extended safety analysis. See 13.2.1.2.

Efficacy study

Using an alpha of 5% and beta of 80% and a 12-month recurrence free survival benefit from 50% till 66% from a recent retrospective study comparing Ox HIPEC vs Oxiri HIPEC for colorectal cancer (figure 1, [6]), 148 patients is needed in each arm. With 10% loss to follow up or violation rate, 163 patients in each arm will be needed. In total, 326 patients are to be included in the colorectal cancer group which will define the sample size.

In total, approximately 341-356 patients will be recruited for the phase I/III trial which will be included from 4 centers with the following estimations:

Uppsala – 114-118 patients

Stockholm – 114-118 patients

Malmö – 57-59 patients

Göteborg – 57-59 patients

Aarhus – patient count pending

Oslo – patient count pending

The CRS and HIPEC operation rate in Sweden is approximately 180 patients/year. Two-thirds are diagnosed with colorectal cancer leaving 120 potential candidates to be included in the study. If we manage a 90% inclusion rate, the dose titration part of the trial will take 6 months followed by another 4.5 years to study efficacy (see 20.5 for further details). The trial program will take approximately 5 years to complete.

##

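### The 140-patient interim review lets OS and RFS results change the primary endpoint, sample size or follow-up, or close the trial, with no arm-blind restriction, no level adjustment and no defined futility criterion

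*Protocol*

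**What the plan says.** Section 13.2.1 (Interim analysis) sets a safety evaluation at 140 randomised patients, 70 per arm, and adds an efficacy review to it: "overall survival and recurrence free survival will be reviewed during this interim safety evaluation to see if a primary endpoint of overall survival is attainable". If OS is judged attainable, depending on the inclusion rate, the primary endpoint changes and a new sample size is calculated. The choice between 3 and 5 years of follow-up is made at the same look. The other outcome is closure: "Alternatively, trial futility will be determined if no differences at all are forthcoming even in the RFS setting". On authority, the section says: "A decision to close the trial is made by the sponsor in conjunction with site investigators".

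Other sections bear on this:

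- The Main efficacy study text in 13.2.1 ties the switch to OS to what the interim results show.
- Section 13.5 words futility differently. It asks for no numerically and clinically relevant difference in RFS, OS, peritoneal RFS or recurrence pattern. Neither wording has a threshold.
- Section 12.4 makes the DMC responsible for "making decision to continue the phase III trial efficacy study after the interim safety evaluation", and 12.5.1 also leaves the interim safety decision to the DMC.
- Section 12.1 has DMC reviews emailed to the site investigators and co-investigators.
- Section 14 notes that the sponsor representative is also the coordinating investigator and that the sponsor has access to source data.
- The synopsis says "Statistical significance will be set at p=0.05", and 13.4 repeats that level. No adjustment for the interim review is stated.

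**The concern.** Three things are at stake.

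**Type I error.** If the primary endpoint or the sample size is chosen after seeing how the arms compare, an unadjusted final test at 0.05 no longer has its nominal chance of a false win for the experimental arm. Nothing in the section limits the review to accrual or pooled counts.

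**Conduct.** Absence of a difference can only be judged between arms. The people named to decide closure therefore need by-arm results, or a report of them, in an open-label trial where they go on selecting, operating on and following patients.

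**Power.** A futility rule with no threshold, applied when few patients have reached 12 months, can close a trial of a treatment that works as planned.

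**Working it through.** **1. The plan's own sample size.** Inputs from 13.3: 12-month RFS 50% versus 66%, alpha 5%, power 80% (written there as beta). Two-sided testing is assumed, since 13.3 does not say.

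- Arcsine formula: h = 2·asin(√0.66) − 2·asin(√0.50) = 0.3257; n = 2·((1.960 + 0.842)/h)² = 148.0.
- Pooled-variance formula: 148.2, rounded up to 149.
- The plan states "148 patients is needed in each arm", so its figure is reproduced. With the 10% allowance, 148 × 1.10 = 162.8, which gives the stated 163 per arm and 326 in total.

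**2. How mature the data are at the look.** Section 20.5 aims for 100 patients per year.

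- The look comes at 140/326 = 43% of enrolment, after 140/100 = 1.4 years.
- Patients with 12 months of follow-up when the 140th enters: 140 − 100 = 40, or 20 per arm.
- Thirty days later, to allow for 30-day morbidity: 140 − 100 × (1 − 30/365) = 48, or 24 per arm. This is 48/326 = 15% of the planned total.

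**3. Type I error if the endpoint choice used by-arm results.** The documents do not give the RFS-OS correlation or the OS information, so these are assumptions: correlation 0.4-0.6, and 15% information on both endpoints. For each endpoint, final z = √t·(interim z) + √(1 − t)·(independent increment), with t = 0.15. The rule simulated under the null keeps whichever endpoint has the larger interim z and tests it at 1.96.

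- Chance of a false win for the experimental arm: 3.5% at correlation 0.4, 3.4% at 0.5 and 3.3% at 0.6, against a nominal 2.5%.
- The two-sided rejection rate stays near 5% under this rule. The error moves towards false wins for the experimental arm.
- If the trial also stops when both interim differences are zero or negative, the figure at correlation 0.5 falls to about 3.1%.
- If the choice uses only accrual and pooled event counts, it remains 2.5%.

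**4. False futility if the design assumption is true (50% versus 66%).** Futility is read here as an observed RFS difference of zero or less.

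- *Only patients with 12-month status.* With X_C ~ Bin(24, 0.50) and X_E ~ Bin(24, 0.66), exact P(X_E ≤ X_C) = 0.161, of which 0.100 is a strictly negative difference. With 20 per arm it is 0.190.
- *All 140 patients' RFS time.* Assumptions: exponential times, uniform accrual, review one month after the 140th patient, recurrence seen when it occurs. Hazards are −ln 0.50 = 0.693 and −ln 0.66 = 0.416 per year, so HR = 0.60 and ln HR = −0.512. With follow-up spread evenly from 1 to 17.8 months, expected events are 27.7 + 18.7 = 46.4. SE = √(1/27.7 + 1/18.7) = 0.299. P(observed HR ≥ 1) = Φ(−0.512/0.299) = Φ(−1.71) ≈ 0.04.
- Requiring OS to show no difference as well makes either figure smaller. Detecting recurrence only at scheduled scans would raise the second somewhat.

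**The case against.** The strongest reply is that the endpoint change is a feasibility decision. It runs one way only, from RFS to OS, with a larger cohort, and depends on the inclusion rate. Accrual and pooled deaths could answer that question. This stands in part: a reader might infer that the trial will pick whichever endpoint looks better, but no sentence says so. The text does not exclude by-arm use either, since the Main efficacy study text points to interim results without saying that they are pooled.

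A reader might also infer that the sponsor and the DMC hold the same decision in flat contradiction. The documents support only a partial conflict. Sections 12.4 and 12.5.1 concern continuation after the safety evaluation, while the closure sentence in 13.2.1 follows the futility rule. What is unreconciled is who sees by-arm efficacy. Sponsor and investigator access is not stated outright; it follows from their deciding on differences, and 12.1 and 14 make it more likely.

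Mitigations exist. Changes go to the regulatory and ethics authorities as an amendment, the interim is unpublished, and the radiologists who determine recurrence are not told the allocation (10.5). None of these restores the error rate once by-arm results have influenced the choice. The updated analysis plan mentioned in 13.2.1 is in an appendix that is not available and might contain an adjustment. That pointer heads the main efficacy text, however, and the interim paragraph stands as current.

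**Conclusion.** The point holds, at modest size. As written, the interim paragraph permits a results-driven change of endpoint, sample size or follow-up with an unadjusted final test, and closure on an undefined between-arm rule by people still running the trial. If by-arm results did drive the switch, one-sided type I error would be about 3.3-3.5% instead of 2.5%, under the assumed correlation, information and selection rule. If only pooled data were used, there would be no inflation.

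The futility rule does not add to type I error; it costs power. Its chance of being met on RFS when the treatment works as planned is about 16% on 24 per arm with 12-month status and about 4% on all RFS time, and lower if OS must also show no difference.

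It would go too far to say that the final 5% test is invalid whatever happens, or to apply the ceiling for unrestricted re-sizing of one endpoint. The section allows only an increase, tied to a new endpoint. The reason to act is that by-arm results, once seen by those running the trial, cannot be unseen.

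**What to change.** Amend the protocol before the 140-patient look, and carry the same rules into the DMC charter.

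- In 13.2.1, state that any change of primary endpoint, sample size or follow-up length rests only on accrual and pooled, arm-blind event counts, and is fixed before any by-arm efficacy table is produced.
- Send by-arm OS and RFS to the DMC only.
- Replace the differing futility wordings in 13.2.1 and 13.5 with one non-binding criterion, set in advance and assessed by the DMC, which passes only a recommendation to the sponsor. The criterion should say which RFS data it uses, since this moves the false-stop risk between about 4% and 16%.
- Reconcile 12.1, 12.4, 12.5.1, 13.2.1 and 13.5 on who sees by-arm results and who takes each decision. In particular, 12.1 should not circulate by-arm efficacy to the sites.

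The cost is wording. The one real loss is that the sponsor can no longer react to by-arm trends.
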